### Sample size

We used effect sizes from the previous literature to determine the sample size. Corpas et al.’s primary care RCT [41] compared both group and individual brief tCBT with TAU for emotional disorders and found low to medium effect sizes for all outcomes. Individual effects were larger (Cohen’s *d* ranged from .54 to .74) than group effects (.4 to .63) when compared with TAU; however, there was no significant difference between both transdiagnostic formats, with (very) low effect sizes (.06 to .27). Another primary RCT by Corpas et al. [36] compared tCBT with TAU and found medium to large effect sizes (from .39 for depression to .81 for panic symptoms). Finally, the PsicAP study compared the group tCBT used herein to TAU in primary care. Intention-to-treat analyses showed low to medium effect sizes over time for depression (Morris’ *d* ranged from .36 to .58), anxiety (.38 to .65), and somatizations (.31 to .4). Subsequently, we decided to assume a medium effect size of .6 (Cohen’s *d*).

Since software to determine sample sizes for linear mixed model analyses was not available, we used the *f* index of G*Power [52]. We assumed an effect size of .3 (the equivalent *f* value); a statistical power (1 - *β*) of .8; and a significance level (*α*) of .05, obtaining a required sample size of 111. However, to control withdrawals and take into account the abandonment rates in other similar trials [36, 41], we assumed a dropout rate of 15%, which brought the required sample size to 128.

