### Statistical methods

#### Analysis of clinical effectiveness

Data analysis will be carried out using SPSS Statistics. Effectiveness-related data will be analysed using intention-to-treat and per-protocol approaches. After the homogeneity of intra- and inter-groups is checked, changes over time (baseline, post-intervention, and follow-ups) in primary and secondary outcomes will be analysed using linear mixed models (LMMs), since this method has been recommended rather than ANOVA or MANOVA analyses because LMMs do not require participants with missing values to be omitted nor imputed, and they are more adequate for repeated measures [95]. Likewise, effect sizes (Cohen’s *d* with bias corrections) will be calculated, as well as their accuracy (by taking into account the number of treatment sessions). The percentage of patients in each cluster who experience a 50% decrease in the number of clinical symptoms and scores to one standard deviation and the percentage of cases with a probable ED before and after receiving treatment (according to cut-off criteria) will be calculated. Therapeutic success criteria will be determined by obtaining post-intervention means significantly lower (*p* ≤ .05) and medium/large effect sizes significantly higher than those of the controls, especially in the ED scores. Clusters will be also compared regarding impairment, quality of life, emotion regulation biases, and satisfaction with treatment.

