#### Analyses of cost-effectiveness and cost-utility

Cost-effectiveness analysis will be conducted by calculating incremental cost-effectiveness ratios (ICERs), which are defined as the difference in mean costs between interventions divided by the difference in their effectiveness according to the participants’ mean scores (i.e., one ICER per each comparison between two clusters and per each instrument). However, cost-effectiveness analyses are open to question since they rate the more appropriate intervention based only on the clinical perspective. Cost-utility analyses use the intervention health-related utilities, subjectively rated by participants. Therefore, they depend on a social perspective, that is, the participants express their preferences based on the value they assign to their health status. The EQ-5D-5L will be used to calculate those utilities as QALYs, and the latter will be used to obtain the incremental cost-utility ratios (ICURs), defined as the difference in mean costs divided by the difference in mean QALYs (i.e., one ICUR per each comparison between two clusters). Since follow-ups will not go beyond 12 months post-intervention, neither costs nor results will be subject to discount. The bootstrapping method (a resampling method) will be used to obtain more accurate ICERs and ICURs. Missing data will be analysed through Student’s *t* and *χ*^2^ tests for ED severity level, sex, and age; this will allow us to know whether missing data due to dropout are related to chance. Finally, a sensitivity analysis will be carried out to test the robustness of cost-effectiveness and cost-utility results.

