Finally, this kind of trial risks a high dropout rate and missing data, especially at follow-ups. Unlike the IAPT programme, the proposed study will not take session-by-session measurements, because the number of instruments we are using would make it difficult. We hope, therefore, that the clinical psychologists will encourage participants to complete the measurements through regular telephone calls. Finally, due to the duration of the study, intervention and measurements might be affected by patients’ availability (holidays, medical appointments, and so on), but we will make an effort to ensure that timings are similar between groups.

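### Tests on severity, sex and age cannot show that dropout is by chance, yet they are the only missing-data step named for the cost and QALY means

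*Protocol article*

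**What the plan says.** The statement is in the protocol article, section Analyses of cost-effectiveness and cost-utility. Missing data are to be examined by t and chi-square "tests for ED severity level, sex, and age", and "this will allow us to know whether missing data due to dropout are related to chance". The plan attaches no consequence to either result.

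The same section defines the estimators that missing data would affect. The ICER is "the difference in mean costs between interventions divided by the difference in their effectiveness according to the participants’ mean scores". The ICUR is "defined as the difference in mean costs divided by the difference in mean QALYs". Both are to be bootstrapped. The section closes by saying that "a sensitivity analysis will be carried out to test the robustness of cost-effectiveness and cost-utility results", without giving the content of that analysis.

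Elsewhere in the article:

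- Analysis of clinical effectiveness prefers linear mixed models for the primary and secondary outcomes because "LMMs do not require participants with missing values to be omitted nor imputed". The section on ICERs and ICURs does not carry this argument over to costs or QALYs.
- Sample size: "we assumed a dropout rate of 15%, which brought the required sample size to 128".
- Anticipated limitations: "this kind of trial risks a high dropout rate and missing data, especially at follow-ups".

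**The concern.** The sentence promises knowledge that the tests cannot supply. A comparison of people with and without data on three observed variables can give evidence against missingness completely at random. It cannot give evidence for it, and it is silent on whether the missing values themselves drove the dropout.

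This matters because cost-effectiveness and cost-utility are the trial's stated aim and the subject of Hypotheses 3 and 4, which Hypothesis 5 carries to 6 and 12 months. The article also gives reasons to expect missingness that is not by chance:

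- It foresees high dropout, especially at follow-up.
- The Discussion says that attrition in the predecessor project with individual therapy was high enough to prevent follow-up.
- The TAU section removes participants whose practitioner recommends psychological treatment. That loss occurs in one arm only and follows the clinical course after randomisation.

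If non-significant tests were taken as reassurance and available cases were then averaged, the ratios could be biased. Bootstrapping would not help, because it addresses sampling uncertainty and not selection.

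**Working it through.** **Inputs.** Sample size: 111 before and 128 after allowance for 15% dropout. The 128 reproduces as 111 × 1.15 = 127.65. Assumed dropout of 15% gives 128 × .15 = 19.2, so about 19 people without data and 109 with. Two-sided alpha is .05; the documents give it for the sample size, and I assume it for these tests. Dropout of 25% and 35% is my assumption, to show the range.

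**Power of the severity t test.** The noncentrality is d / √(1/n₁ + 1/n₂), and power comes from the noncentral t with n₁ + n₂ − 2 = 126 degrees of freedom (critical value about 1.979).

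For 19 against 109, √(1/19 + 1/109) = .2486:

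| Difference d (SD) | Noncentrality | Power |
|---|---|---|
| .3 | 1.21 | .22 |
| .5 | 2.01 | .51 |
| .6 | 2.41 | .67 |
| .7 | 2.82 | .80 |

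For d = .5 at higher dropout:

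| Dropout | Split | √(1/n₁ + 1/n₂) | Noncentrality | Power |
|---|---|---|---|---|
| 25% | 32 vs 96 | .2041 | 2.45 | .68 |
| 35% | 45 vs 83 | .1851 | 2.70 | .76 |

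For sex, with assumed proportions of 50% and 70%, chi-square power at 19 against 109 is .41.

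**Would more power rescue the inference?** No. This was illustrated by a simulation of 4,000 trials of 128 people in three arms. Its assumptions do not come from the documents: no true arm difference; dropout unrelated to severity, sex and age; poor responders leaving the therapy arms and good responders leaving TAU, at a log-odds of 1 per SD of response.

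- All three tests were non-significant in about 86% of trials. That is what three independent 5% tests give by chance (.95³ = .857).
- The difference between one therapy arm and TAU among people with data was biased by .27 SD at 15% dropout and by .47 SD at 28%.
- In the trials where all three tests were non-significant, the bias was the same: .27 and .47 SD.

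Under this mechanism, passing the tests carries no information about bias. The sizes belong to the assumed mechanism and are not a forecast for this trial.

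**The case against.** The strongest reply is that one sentence overclaims and the rest is detail that a condensed article may leave to an analysis plan. Several parts of it stand.

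- **No rule links the tests to the analysis.** A reader might infer that a non-significant result will clear complete-case means. The article never says so, nor does it say that ICERs and ICURs will use complete cases. The consequence must therefore be stated conditionally.
- **Timing and pooling are open.** A reader might assume that the tests use baseline severity and pool the arms. The text specifies neither, and severity is measured at all four time points.
- **Totals are not lost at every missed visit.** A reader might infer that costs and QALYs are undefined for anyone who misses one assessment. But Cost analysis draws on medical records as well as questionnaires, so record-based costs can survive a missed visit. The EQ-5D is described under Secondary outcomes, so it could fall within the mixed model's scope, and visit means from that model could yield mean QALYs. The article does not say that QALYs will be built this way.
- **The share with all four visits is unknown.** A reader might conclude that it will be below 85%. The article does not say to which time point the 15% applies.
- **Retention is planned.** Collection process invites people who leave treatment to keep completing questionnaires, though with emphasis on the first post-treatment assessment, and allows several modes of completion. Stopping treatment is not the same as missing data.
- **Power improves with dropout.** The low-power argument weakens in the very situation where missing data matter most.

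None of this makes the sentence true. An unseen analysis plan could add methods, but it could not turn these tests into proof that dropout is by chance.

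**Conclusion.** The point holds as an error of stated inference. The tests cannot establish that dropout is by chance. At the assumed 15% dropout their power for a half-SD severity difference is .51 (.68 to .76 at 25% to 35%), and even full power would leave dependence on unobserved costs or utilities untested.

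The consequence is conditional. These tests are the only missing-data step named for mean costs and QALYs. If they were used to justify available-case means, the ICERs and ICURs could be biased, chiefly through the EQ-5D and self-reported cost items. The documents do not establish that such bias will occur, or how large it would be. The power figures rest on the 15% assumption and a two-sided 5% test; the simulated bias rests entirely on an assumed dropout mechanism.

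This should be corrected before outcome data are examined. The mixed-model analysis of clinical effectiveness does not depend on it.

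**What to change.** 1. Keep the t and chi-square tests as a description of who has missing data, and delete the claim that they will show whether dropout is by chance.
2. State that the primary economic analysis handles missing EQ-5D and cost items under missing at random. One suitable method is multiple imputation by arm, using baseline and observed follow-up data as predictors, combined with the planned bootstrap.
3. Use the sensitivity analysis already planned to include a missing-not-at-random scenario that may differ by arm, for example with imputed utilities worsened and imputed costs raised.

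The cost is a change of wording, some extra programming and possibly wider intervals. No new data are needed.

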### Monitoring

The proposed trial has no data monitoring committee since the potential harms are limited to the pharmacological treatment that is ordinarily provided in primary care. Study progress will be supervised through regular contacts and meetings between the intervention professionals and the principal investigator. All updates will be published through the online registers: ClinicalTrials.gov (NCT04847310) and Protocols.io (bx2npqde).

## Discussion

This protocol tries to combine the strengths of the PsiBrief and the PsicAP projects. The large PsicAP project [34, 35] studied a brief group transdiagnostic intervention as a more cost-effective possibility for ED treatment in primary care; however, as has been noted, group therapy is less flexible (and less popular amongst patients) than individual therapy (which allows for stronger therapeutic relationships). Meanwhile, the PsiBrief project [40, 41], which introduced individual therapy, saw a high attrition rate, so follow-ups were not possible. Also, it did not include cost-benefit analyses. The proposed study will try to combine the best of each of these projects, comparing the cost-effectiveness and cost-utility of both group and individual transdiagnostic therapy with TAU in primary care.

Based on PsiBrief and PsicAP’s results, we hypothesize that our proposed experimental interventions will be equally effective in reducing emotional symptoms and improving emotion regulation strategies, and TAU will be the least effective. Since group therapy involves several patients with different symptoms, we hypothesize that it will have the best outcomes in terms of cost-effectiveness and cost-utility, and TAU the worst. Finally, we hypothesized that these results will be sustained in the follow-ups.

### Anticipated limitations

We recognize that our protocol has several limitations, and we expect difficulties in its execution. First, the trial design excludes some groups to minimize confusion variables (minors, older people, and patients with severe mental disorders and/or with intellectual, legal, or high functional disability), so additional research will have to be carried out on these populations; and the single-blind approach will not allow us to control patients’ therapy expectations, though participant blinding is ordinarily not feasible in RCTs that compare psychotherapies.

Second, we might encounter obstacles during recruitment. In the first phase, the great care saturation faced by GPs (i.e., they have to deal with great numbers of patients in a short time) might make enrolment difficult; moreover, since there has never been a psychotherapy culture in primary care, some of them might have little motivation to collaborate. In the second phase, the main limitation might be the measurement tools. Brief instruments have been included in the protocol because primary care requires rapid assessment; however, they do not have the same diagnostic accuracy as gold-standard tools such as the SCID. Furthermore, because these questionnaires are self-administered, completion and the veracity of answers are less controlled than clinical interviews. Nonetheless, the tools included have been validated and tested in Spanish primary care, and they accelerate the diagnostic process in clinical practice.

Third, the interventions might have limitations. For example, each treatment may have a different duration, especially TAU, so this might impact effectiveness (though we will consider this in our analyses). Also, each intervention will be carried by different personnel (i.e., GPs and clinical psychologists), so this might affect the results. In addition, TAU might generate expectations in participants, and they cannot be feasibly blinded. An alternative may be sham therapy, but TAU is closer to clinical reality, so it provides better external validity. The level of adherence to the protocol is another difficulty envisaged, though the therapists will be supervised by PhD trainers during the treatment period.

Finally, this kind of trial risks a high dropout rate and missing data, especially at follow-ups. Unlike the IAPT programme, the proposed study will not take session-by-session measurements, because the number of instruments we are using would make it difficult. We hope, therefore, that the clinical psychologists will encourage participants to complete the measurements through regular telephone calls. Finally, due to the duration of the study, intervention and measurements might be affected by patients’ availability (holidays, medical appointments, and so on), but we will make an effort to ensure that timings are similar between groups.

### Future directions

If our results show the economic feasibility of including psychotherapy in primary care, they may help to change health care policies and implement empirically-supported psychological treatments following a stepped-care model. Patients with mild to moderate conditions would be treated in primary care and those with severe mental disorders would be referred to specialized care involving more intensive therapies that combine psychological and pharmacological approaches. As a result, primary care resources would be optimized, waiting lists would be unblocked, and patients would spend less time of their lives with their disability. Once such a model is implemented, the next step might be the development of internet-based psychotherapies through the use of websites or apps, which may be more cost-effective and accessible for some people.

However, even though empirically-supported psychotherapies may improve patients’ symptoms and quality of life, they cannot reduce prevalence rates; only prevention can do that. Investment is needed both in psychological treatment and prevention. If we can resolve people’s mental problems before they become disorders, we might save not only costs but also a great deal of suffering.

#### Protocol status

This project started in September 2021.

## Data Availability

Datasets generated and analysed during the proposed study will be available from the corresponding author on reasonable request.

## Abbreviations

ED: Emotional disorder
CBT: Cognitive-behavioural therapy
CDTE: Questionnaire of Cognitive Distortions in Emotional Disorders
CERQ: Cognitive Emotion Regulation Questionnaire
CIDI: Composite International Diagnostic Interview
DDD: Defined daily doses (per 1000 habitants)
DSM: Diagnostic and Statistical Manual of Mental Disorders
EQ-5D-5L: 5-domain, 5-level European Quality of Life Scale
GAD: Generalized anxiety disorder
GP: General practitioner
IACTA-PB: Inventory of Cognitive Activity in Anxiety Disorders-Panic Brief version
IAPT: Improving Access to Psychological Therapies
ICD: International Classification of Diseases
ICER: Incremental cost-effectiveness ratio
ICUR: Incremental cost-utility ratio
LMM: Linear mixed models
MCQ-NB: Metacognitions Questionnaire-Negative Beliefs subscale
MDD: Major depression disorder
NICE: National Institute for Health and Care Excellence
OECD: Organisation for Economic Co-operation and Development
PD: Panic disorder
PHQ: Patient Health Questionnaire
PSWQ-A: Penn State Worry Questionnaire-Abbreviated
QALY: Quality-adjusted life year
RCT: Randomized controlled trial
RRS-B: Ruminative Responses Scale-Brooding subscale
SCID: Structured Clinical Interview for DSM
SDS: Sheehan Disability Scale
TAU: Treatment as usual
tCBT: (brief) transdiagnostic cognitive-behavioural therapy
UP: Unified Protocol for the Transdiagnostic Treatment of Emotional Disorders
WHOQOL: World Health Organization Quality of Life Instrument
